### Conceptual framework

The conceptual framework, linking heat exposure, modifying factors, maternal and fetal physiological responses, and pregnancy outcomes, is depicted in Fig. 2. The primary exposure is environmental heat. The extent to which heat impacts health may vary depending on maternal factors (socio-demographic and health-related characteristics) and modifiable behaviors (physical activity, hydration status, and environmental exposure). Together, these characteristics and behaviors influence the physiological response to heat, which in this study is assessed through fetal strain, maternal heat strain and sleep quality. The physiological response could in turn affect birth outcomes such as birth weight, the gestational age at birth and the occurrence of stillbirth.

**Fig. 2 Fig2:**
[figure not shown]
Causal pathway for linking heat exposure, modifiers (maternal factors and behavior) with the physiological response (maternal and fetal) with pregnancy outcomes

### Measurement methods

The Physio-HeMAB study aims to provide a comprehensive view of the dynamic interaction between maternal physiology, fetal strain, and environmental heat stress. Therefore, socio-demographic and clinical data will be collected during antenatal care, wearable devices will continuously measure maternal physiological parameters, and environmental sensors will continuously log heat stress.

#### Data obtained at the health care facility

A gynecologist will ascertain gestational age through the last menstrual period or the biparietal diameter, measured by ultrasound. Doppler ultrasound recordings of the umbilical artery, middle cerebral artery, and cerebroplacental ratio; as well as cardiotocography recordings of the fetal heart rate, will also be measured at consultations. During these visits, standard clinical measurements (tympanic temperature, pulse, and blood pressure) will be recorded, and a questionnaire on maternal factors including socio-demographic characteristics and health indicators, will be completed. Questionnaires on daily routines, fluid intake, and sleep logs will be administered to complement the wearable device measurements. Participants’ feedback on the acceptability and perceived burden of the study procedures will be obtained in the closing questionnaire. Birth outcomes will be evaluated post-partum using patient records.

#### Data collected by sensors

Five sensors will collect data over a seven-day study period for each participant (Table 1: Device specifications).

**Table 1 Tab1:** Device specifications

DEVICE	GENEActiv Original	Bittium Faros™ 180	Calera Research	Hygrometer PCE-WB 20SD	SwitchBot Meter
COMPANY	ActivInsights, United Kingdom	Bittium Biosignals Ltd., Finland	greenTEG AG Switzerland	PCE Instruments UK Ltd., United Kingdom	SWITCHBOT INC, USA
MEASURE-MENT	Three-axial Acceleration, Near body temp., Ambient light	ECG, Acceleration	Estimated CBT, Skin temp., Acceleration	WBGT	Air temp., Humidity
TYPE OF SENSOR	Wearable motion sensor	Biomedical wearable electro-cardiogram	Skin temperature and heat-flux monitor	Environmental heat stress meter	Environmental sensor
RESOLUTION	100 Hz	250 Hz	17 mHz	17 mHz	17 mHz
DATA TRANSFER	Cradle with USB cable	Micro-USB cable	Bluetooth BLE	SSD Card	Mobile Phone Application
DATA FORMAT	BIN	EDF	CSV	CSV	CSV

##### Physiological data

Continuous physiological data will be collected with research-grade wearable devices. These wearables are: (1) an Electrocardiography (ECG) device (Bittium Faros™ 180) to record maternal cardiac electrical activity and derive maternal heart rate (HR) and heart rate variability (HRV). (2) A core body temperature sensor (Calera Research), which derives core body temperature (CBT) from continuous monitoring of skin temperature and heat flux, and (3) an accelerometer (GENEActiv Original) for continuous three-axial accelerometry recordings, to assess physical activity and sleep.

##### Temperature data

Heat and heat stress will be observed at individual and regional levels. On the individual level, participants will receive 4) Hygrometers (PCE-WB 20SD) to be placed outside their homes and measure Wet-Bulb Globe Temperature (WBGT) wherever feasible. 5) Switch Bot Meters (SwitchBot) will record home indoor air temperature and humidity. For regional observations of the Navrongo Upper East Region, retrospective Universal Thermal Climate Index (UTCI) data from the ERA5 data set provided by the Copernicus Climate Data Store [48] will be utilized.

### Measured variables

In alignment with the conceptual framework, exposure, covariables, and outcomes are specified in Table 2.

**Table 2 Tab2:** Expected outcome categories, relevant outcome measures, variable types, measurement method and level of analysis

CATEGORY	MEASURE	VARIABLE TYPE	MEASUREMENT METHOD
EXPOSURE			
Environmental measurements	WBGT	Continuous	Hygrometer PCE-WB 20SD
	Air temperature and humidity	Continuous	SwitchBot Meter
	UTCI	Continuous	ERA5 data set
COVARIATES/ CONTEXT			
Maternal factors	Socio-demographic factors	Categorical/ Continuous	Questionnaire, Clinical record
	Health indicators	Categorical/ Continuous	Questionnaire, Clinical record, Physical examination
	Modifiable behaviors	Categorical	Questionnaire
Physical activity	Time- and temperature-specific physical activity	Continuous	GENEActiv Original, Hygrometer PCE-WB 20SD, Activity diary
	Domain-specific physical activity	Categorical	Activity diary
Study-related	Intervention status	Binary	Study assignment
OUTCOMES			
Maternal heat strain	HR and HRV Physiological Strain Index	Continuous Continuous	Bittium Faros™ 180 Bittium Faros™ 180, Calera Research
	Self-reported heat strain symptoms	Categorical	Questionnaire
Sleep quality	Sleep duration	Continuous	GENEActiv Original, Self-reported sleep-log
	Self-reported sleep quality	Score	Self-reported sleep-log
Fetal strain	Fetal HR	Continuous	Cardiotocography
	Umbilical artery and middle cerebral artery Doppler parameters	Continuous	Doppler ultrasound
	Cerebroplacental ratio	Continuous	Doppler ultrasound
Neonatal health	Birth weight	Continuous	Clinical record
	Gestational age at birth	Continuous	Clinical record
	Stillbirth	Binary	Clinical record

### Participant timeline

Participants will be enrolled in a seven-day monitoring period. Physiological and behavioral data will be continuously collected with wearable sensors and a self-logged activity diary. Environmental sensors will measure on individual level throughout the week. Participants visit their health facility on days one, four, and seven. Study procedure details and activity flow are depicted in Fig. 3.

**Fig. 3 Fig3:**
[figure not shown]
Study timeline. Seven-day continuous monitoring period with three scheduled clinic visits. Pt = Part, Qs= Questionnaires

Participants are encouraged to continue all components of data collection throughout the seven-day monitoring period, as this will capture more diverse exposure to environmental stressors. However, participants are given the option to terminate the trial on day four, in which case final study procedures will be conducted on day four instead of day seven.

### Sample size and selection of subjects

The sampling method will be consecutive sampling of women who visit any of the four purposefully selected HDSS health facilities for antenatal consultations. Consideration will be made for pregnant women who can conveniently attend the health facility at least three times during the physiological measurement period. Inclusion criteria are (1) being a pregnant woman in the third trimester (> 28 weeks) with a (2) singleton pregnancy. Further inclusion criteria are (3) being of legal age, (4) able to give consent, (5) registration (having an ANC card) and (6) living within 10 km proximity of one of the four selected HDSS health facilities. Exclusion criteria are (1) illness that requires hospital admission or immediate delivery, (2) known fetal malformations, and 2) a known psychological or mental health concern.

The primary outcome variable is maternal heart rate (beats per minute, bpm), which serves as a physiological proxy for maternal heat strain, reflecting cardiovascular responses to heat exposure. To determine an appropriate sample size for the Physio-HeMAB study, a power analysis was conducted for comparing mean heart rates between two independent groups. Assuming a mean detectable difference of 5 bpm, a common standard deviation of 10 bpm, a two-sided significance level (α) of 0.05, and 80% statistical power, the required sample size is 63 per group. The study will enroll 200 participants in total across the four HDSS health facilities, 100 in the intervention group and 100 in the control group. As this is the first time this type of study will be conducted in this setting, it is not yet possible to precisely estimate potential attrition, data loss and inter-individual variability. Therefore, the sample size is chosen to provide a conservative margin, ensuring that even with 30% attrition, the study retains adequate power to detect clinically relevant differences in heart rate between groups.

Participants will be invited to provide feedback on the acceptability and perceived burden of study procedures as part of the Patient and Public Involvement strategy, to help refine future implementation and promote inclusive participation that builds trust in the research institution. To promote participant retention, participants will benefit from enhanced assessments of well-being during pregnancy, including an additional ultrasound scan. In the case of incidental findings, participants who choose to be informed will be referred for additional diagnostic evaluations. The study team will cover transportation and treatment costs in accordance with local standards, and participants will receive soap and refreshments.

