### Study design

Physio-HeMAB is an interventional, cluster-randomized substudy embedded within the larger parent HeMAB trial (PACTR202510765394928). In the parent trial, the heat adaptation strategy (intervention) is allocated to 16 health centers (HCs) through cluster randomization. The primary outcome of the larger HeMAB study is the change in birth weight, assessed in the 3,200 births annually in the study area (*n* = 1,600 per cluster).

Physio-HeMAB does not conduct randomization itself; however, it uses the pre-existing randomized allocation within the existing trial framework to evaluate intervention effects on physiological outcomes. Therefore, by definition, Physio-HeMAB constitutes an interventional study with a cluster-randomized design. The HeMAB study design is visualized in Fig. 1.

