**Fig. 1 Fig1:**
[figure not shown]
Overview of the Physio-HeMAB study nested within the larger healthy mamas and babies (HeMAB) trial

Within this framework, Physio-HeMAB applies prospective physiological monitoring to assess maternal and fetal responses to environmental heat in both intervention and control clusters. Each Physio-HeMAB cluster comprises two health facilities (one hospital and one affiliated health center), purposefully selected to ensure comprehensive data collection. At the hospital level, permanent gynecologists perform ultrasound examinations, with support from midwifery staff. The associated health centers are operated by trained midwives who deliver essential maternal and reproductive health services.

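### Neither eligibility nor 'Intervention status' is tied to the woman's own randomised health center, so hospital attenders from opposite-arm or non-trial health centers can be enrolled and may be misclassified

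*Protocol article*

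**What the plan says.** Study design, in the Protocol article, names one kind of randomised unit: "the heat adaptation strategy (intervention) is allocated to 16 health centers (HCs) through cluster randomization". Physio-HeMAB does no randomisation itself; "it uses the pre-existing randomized allocation within the existing trial framework to evaluate intervention effects on physiological outcomes".

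The text after Fig. 1 then uses a different unit: "Each Physio-HeMAB cluster comprises two health facilities (one hospital and one affiliated health center), purposefully selected to ensure comprehensive data collection". It speaks of intervention and control clusters in these terms. It does not say that the hospitals were randomised, or that everyone attending a hospital receives its pair's strategy.

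Sample size and selection of subjects describes recruitment as "consecutive sampling of women who visit any of the four purposefully selected HDSS health facilities for antenatal consultations". The residence criterion is "living within 10 km proximity of one of the four selected HDSS health facilities". The other inclusion criteria are third trimester, singleton pregnancy, legal age, ability to consent, and registration shown by an ANC card. The card is not required to come from any particular health center.

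Table 2 lists the arm variable as "Intervention status Binary Study assignment", with no rule for deriving it.

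**The concern.** A cluster-randomised comparison needs each participant to belong to a randomised unit and to be analysed under that unit's allocation. Here the randomised unit is the health center, while the recruiting unit is a hospital-plus-health-center pair with an eligibility radius drawn around facilities. A hospital can also see women whose own health center is another one. Under the stated criteria such a woman qualifies, whether her center is in the same arm, in the opposite arm or outside the parent trial.

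If her arm is then read off the facility where she was recruited, an opposite-arm woman carries the wrong label. A non-trial woman recruited at the intervention pair is labelled as exposed to a strategy that her center was not allocated. Both kinds of error normally pull the difference in heart rate towards zero. They would also weaken the intervention-by-heat interaction described under Statistical methods, which uses the same arm variable. A null result could then not be told apart from mislabelling. If the home health center is not recorded at enrolment, it may be hard to recover later.

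**Working it through.** **Does the text allow it?** Take a woman whose health center is in the control arm and who attends antenatal care at the hospital of the intervention pair.
- Recruitment: she attends one of the four facilities, so she is in the sampling frame.
- Residence: she qualifies if she lives within 10 km of that hospital, or of any other of the four.
- Registration: any ANC card satisfies the criterion.
- Catchment or arm: no criterion applies.

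She is eligible. The same holds for a woman whose center is not one of the 16.

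**Which arm would she get?** Study design points to the parent allocation, which would give control. The text after Fig. 1 treats the facility pair as the cluster, and the sample-size text enrols 100 per group across the four facilities; that suggests intervention. Table 2 does not settle it.

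**Inputs from the protocol.** Difference 5 bpm, SD 10 bpm, two-sided alpha 0.05, power 80%, 63 per group required, 100 per group enrolled, 30% attrition (100 × 0.70 = 70 per group left).

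**Reproducing the plan's figure.** n = 2(1.960 + 0.842)² × 10² / 5² = 62.8, so 63 per group, as stated. Power at n per group is Φ(5 / (10√(2/n)) − 1.960), which gives 84% at 70 and 94% at 100. This treats women as independent, as the protocol's calculation does.

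**Effect of misclassification.** The share q is not in the document and is assumed here.
- Both arms contain a share q of opposite-arm women: the expected difference is 5(1−2q).
- Only the intervention arm contains a share q of unexposed women: the expected difference is 5(1−q).

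| q | Both arms: difference (bpm) | n per group for 80% | Power at 70 | Power at 100 | Intervention arm only: difference (bpm) | Power at 70 |
|---|---|---|---|---|---|---|
| 0% | 5.0 | 63 | 84% | 94% | 5.00 | 84% |
| 5% | 4.5 | 78 | 76% | 89% | 4.75 | 80% |
| 10% | 4.0 | 99 | 66% | 81% | 4.50 | 76% |
| 20% | 3.0 | 175 | 43% | 56% | 4.00 | 66% |

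Power based on the t distribution is up to about one point lower (65% and 42% at 70 per group for q = 10% and 20% in both arms).

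**Margin before 80% is lost.** At 70 per group, the difference detectable with 80% power is 2.802 × 10 × √(2/70) = 4.74 bpm. Setting 5(1−2q) = 4.74 gives q of about 2.6% in both arms. Setting 5(1−q) = 4.74 gives about 5.2% in the intervention arm alone.

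**The case against.** The strongest reply is that the article never says arm follows the recruiting facility. It says that the substudy uses the existing randomised allocation, and Table 2's entry is compatible with coding by the woman's own health center. The full protocol or the parent-trial protocol may state that rule. This stands in part. A reader might infer that women are in fact counted in the wrong arm, or that the randomised allocation no longer defines the groups; the document supports neither statement. What it does show is a stated eligibility rule that does not look at arm, beside a redefined cluster that makes coding by facility the natural reading.

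Three further points stand.
- Women from other health centers in the same arm carry the correct arm label. Only opposite-arm and non-trial women are at issue.
- No distances, catchment boundaries or hospital locations are given. A reader might infer that the 10 km circles of the two arms overlap, but if the pairs lie more than 20 km apart they do not. Any estimate of q from land area would rest on assumptions that the article cannot support.
- Limiting recruitment to the catchment of the pair's health center could be costly. With 3,200 births a year over 16 centers, assumed equal, each has about 200. Over one six-month dry season and a 12-week third trimester (both assumed), about 200 × (26 + 12)/52 = 146 women per center would pass through the eligible period, and 100 per arm would have to be enrolled from them.

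The last point weighs against that remedy, not against recording and coding by home health center.

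**Conclusion.** The concern holds as a gap between the unit of randomisation and the rules for eligibility and arm. The article lets women from opposite-arm or non-trial health centers enter through the hospitals, and it does not fix their intervention status by their own center's allocation. Misclassification is a risk that the criteria permit, not an event that they show, and it arises only if arm is taken from the facility pair.

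Its size is unknown. The power figures depend on an assumed q, on the full 5 bpm effect in correctly classified women and no effect in unexposed women, and on the protocol's own omission of clustering. Within those limits, the margin is thin: after the planned 30% attrition, about 5% opposite-arm women in each arm bring power to about 76%, against the protocol's assurance of adequate power. If only the intervention arm is affected, the difference shrinks half as fast and it takes about 10% to reach the same point.

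**What to change.** 1. At enrolment, record each woman's home health center from the ANC card and HDSS residence.
2. Define 'Intervention status' in Table 2 as the parent-trial allocation of that health center, not of the facility where she was recruited.
3. Add an exclusion for women whose health center is not one of the 16 in the parent trial.
4. Add a sensitivity analysis restricted to women who belong to the randomised health center of the pair.

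The cost is one extra recorded field, a few excluded hospital attenders, and possibly slightly unequal arm sizes, because arm will no longer be fixed by recruiting site. Restricting all recruitment to the pair's catchment is optional and may slow enrolment materially. The recording should start before or during enrolment.

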## Discussion

Physio-HeMAB is a comprehensive, non-invasive, multi-level physiological assessment designed to capture the complex interplay between environmental heat exposure, maternal physiological responses, and fetal health during pregnancy. A key strength of the study is the integration of continuous environmental monitoring, wearable-based maternal physiological measurements, and fetal assessments within a single analytic framework. Conducting the study within the Navrongo HDSS enables data collection under real-world living and working conditions, enhancing ecological validity and policy relevance. As a sub-study embedded within the larger HeMAB parent trial, Physio-HeMAB leverages the cluster-randomized implementation of a gender-transformative heat adaptation strategy to compare physiological responses between exposed and unexposed participants. This design strengthens the study’s relevance for adaptation policy by linking physiological evidence to a real-world public health intervention. Importantly, the study addresses a critical evidence gap, as most existing heat-related interventions and early warning systems are not tailored to pregnant women, and physiological evaluations of adaptation strategies in this population remain scarce.

Limitations include that the seven-day monitoring period per participant may not fully capture longer-term variability in heat exposure, behavioral adaptation, or physiological responses. Operationally, Physio-HeMAB is the first study of its kind conducted in this specific setting and with pregnant women. As such, uncertainties remain regarding participant retention, data completeness, inter-individual variability, and the performance of the multiple wearables and environmental sensors under field conditions. To address these challenges, the study deliberately enrolls a larger sample than required for the primary outcome, implements retention-enhancing procedures, and applies rigorous data quality control protocols.

Physio-HeMAB is designed to generate valuable methodological and physiological insights. By linking individual-level physiological responses to environmental heat exposure and adaptation strategies, the study supports the evidence base for the development of context-specific, gender-responsive, and scalable public health interventions aimed at protecting maternal and fetal health in a warming climate.

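### The power claimed for the between-arm heart-rate comparison assumes independent women, although the intervention is allocated by cluster and only four facilities recruit

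*Protocol article*

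**What the plan says.** All references are to the Protocol article.

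- **Sample size and selection of subjects.** The primary outcome is maternal heart rate, and "a power analysis was conducted for comparing mean heart rates between two independent groups". The inputs are a difference of 5 bpm, "a common standard deviation of 10 bpm", "a two-sided significance level (α) of 0.05" and 80% power, giving 63 per group. Enrolment is 200 women at four purposefully selected facilities, 100 per arm. The larger number is explained by uncertain attrition, data loss and inter-individual variability, "ensuring that even with 30% attrition, the study retains adequate power to detect clinically relevant differences in heart rate between groups".
- **Study design.** The parent trial allocates the intervention to 16 health centers by cluster randomization, and the section concludes that "Physio-HeMAB constitutes an interventional study with a cluster-randomized design". Each Physio-HeMAB cluster is described as one hospital plus one affiliated health center.
- **Statistical methods.** A multi-level framework is announced. Linear mixed models with random intercepts are specified for repeated measurements. The level of the intercept is not named.
- **Discussion.** The reassurance is repeated: "the study deliberately enrolls a larger sample than required for the primary outcome".

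**The concern.** The calculation and the design do not match. A two-sample formula for independent women ignores the correlation between women at the same facility and the small number of units that carry the allocation. Recording heart rate repeatedly within each woman does not remove variation between facilities.

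The article gives the whole calculation and draws a firm conclusion from it, so this is not a detail that a condensed article leaves to a fuller document. At stake is how the between-arm heart-rate result is read. A null result would be taken as coming from an adequately powered comparison. If the analysis also ignored clustering, a positive result would carry more than the nominal 5% error.

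**Working it through.** **Inputs from the article:** difference 5 bpm, SD 10 bpm, two-sided alpha 0.05, power 80%, 100 enrolled per arm, 30% attrition, four facilities.

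**Assumptions:** two facilities per arm, inferred from four facilities and equal arms; and the ICC, which the article does not give and which is therefore shown over a range.

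**1. The plan's own figure.** n = 2 × (1.96 + 0.8416)² × 10² / 5² = 62.8, rounded up to 63 per group. It reproduces exactly with no design effect, so none was applied.

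**2. The margin.** 63 / 0.7 = 90, so enrolling 100 covers 30% attrition. It leaves 100 × 0.7 = 70 per arm, 7 above 63. Under independence, 70 per arm gives 84% power.

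**3. Adding clustering by facility.** With m women per facility, the design effect is DE = 1 + (m − 1) × ICC. The standard error of the arm difference is √(2 × 100 × DE / n), and large-sample power is Φ(5/SE − 1.96). At 70 per arm m = 35; at 100 per arm m = 50.

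| ICC (assumed) | DE at m = 35 | SE at 70 per arm | Power, 70 per arm | Power, 100 per arm |
|---|---|---|---|---|
| 0 | 1.00 | 1.69 | 84% | 94% |
| 0.01 | 1.34 | 1.96 | 72% | 82% |
| 0.02 | 1.68 | 2.19 | 63% | 71% |
| 0.05 | 2.70 | 2.78 | 44% | 48% |

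**4. Break-even ICC for 80% power.** Solve n / DE = 62.8.
- 70 per arm: (70/62.8 − 1) / 34 ≈ 0.0034.
- 100 per arm: (100/62.8 − 1) / 49 ≈ 0.012.

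**5. Required size with the four facilities fixed.** Here m grows with n, so n = 62.8 × [1 + (n/2 − 1) × ICC], which gives n = 62.8 × (1 − ICC) / (1 − 62.8 × ICC / 2).
- At ICC 0.01: 62.8 × 0.99 / 0.686 ≈ 91 per arm retained.
- The denominator reaches zero at ICC = 2/62.8 ≈ 0.032. Above that, no number of women at these facilities gives 80%.

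**6. Few units (illustration).** Four facilities in two arms leave 4 − 2 = 2 between-facility degrees of freedom. From the noncentral t distribution with 2 df and noncentrality 5/SE, power at 70 per arm is 38% at ICC 0, 31% at 0.01 and 19% at 0.05. At 100 per arm it is 48%, 37% and 20%.

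**7. A test that ignores clustering.** True type I error is 2 × [1 − Φ(1.96/√DE)]. With m = 35 this is about 9% at ICC 0.01 (DE 1.34) and 23% at ICC 0.05 (DE 2.70).

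**The case against.** The best defence has four parts, and some of it stands.

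- **The ICC may be very small.** It is not in the article, so the size of the loss is conditional. On the large-sample view, 80% survives at 70 per arm up to an ICC of about 0.0034, and at 100 per arm up to about 0.012. That stands. But the article neither states nor justifies so small an ICC, and its assurance is made at 30% attrition.
- **Mixed models are planned.** The random intercepts are given for repeated measurements, and no facility or cluster level is named. If one were added, it would rest on four units, which brings the power problem into the open and does not solve it.
- **The 2-df powers belong to a test the article does not name.** Correct. They show what four facilities can support and are not the power of the planned analysis.
- **The primary objective also concerns heat exposure.** True. The association of heat with heart rate within women is less affected. But the objective covers heat exposure with and without the strategy, and the power statement is explicitly about the difference between groups.

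Some stronger readings are tempting but not supported:

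- **The attrition allowance uses up the whole margin.** It does not: 70 are retained against 63. The slack is small, not nil.
- **A larger sample would solve it.** Multiplying 63 by the design effects at m = 35 suggests 84 to 170 per arm. That holds m fixed while n grows. With four facilities the need is about 91 at ICC 0.01, and 80% is out of reach at 0.05.
- **There is certainly one cluster per arm.** The two-facility clusters in Study design suggest it, but the mapping to arms is not stated and the figure is not shown. The same section also uses the word loosely, giving 1,600 births per cluster out of 3,200.
- **The trial's test will exceed 5% error.** That presumes an analysis without a cluster term, which the article does not specify.

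**Conclusion.** The concern holds for the between-arm heart-rate contrast. The arithmetic behind 63 is right; it is applied to the wrong design. The claim of adequate power at 30% attrition is not supported, because clustering was given no allowance and only 7 women per arm remain above the independent-sample requirement.

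Assuming two facilities per arm, large-sample power after attrition is 72% to 44% for ICC 0.01 to 0.05, against the 84% that independence would give. That range is an assumption. What does not depend on the ICC is that a test on 2 between-facility degrees of freedom misses 80% at every value, including zero. If the two-facility clusters do mean one cluster per arm, intervention is confounded with cluster and no cluster-level test exists. The article leaves that open and should settle it.

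**What to change.** Change the text in Sample size and selection of subjects, and in the Discussion:

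1. Say that 63 per group gives 80% power only if women are independent.
2. State how many facilities and clusters are in each arm, and show power over an assumed ICC range with that number, labelled as an assumption.
3. Withdraw the assurance of adequate power at 30% attrition, and the statement that the sample exceeds what the primary outcome requires, as far as they concern the between-arm contrast.
4. Present that contrast as exploratory, with interval estimates that reflect the facility or cluster level. If there is one cluster per arm, say that the intervention effect cannot be separated from cluster differences.

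No extra enrolment is proposed, and more women at the same four facilities might not restore 80% in any case. The cost is rewording and a less favourable stated power.
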